## Abstract

**Background:**

The prevalence of childhood obesity and diabetes continues to rise in the United States (US), especially among minority populations. The objective of the Early Tracking of Childhood Health Determinants (ETCHED) study is to investigate the role of adverse fetal and early-life risk exposures that contribute to the development of childhood obesity and metabolic risk.

**Methods:**

ETCHED is a longitudinal observational study of American Indian/Alaska Native (AI/AN) and Hispanic pregnant woman and their offspring. Pregnant mothers ≥ 18 years old are enrolled at a large public hospital system in the southwestern US. Enrolled mothers are followed through pregnancy, delivery, and the maternal/offspring dyad will be followed until the child’s 18th birthday. At each maternal visit, questionnaires assessing medical history, diet, physical activity, sleep, perceived stress, and socioeconomic and sociocultural information are obtained. Standard laboratory tests during maternal visits include glycemic measures, lipids, and renal function. Additional bio samples obtained include venous blood samples and cord blood for obesity/metabolic biomarkers and genetic/epigenetic testing, urinalysis, placental tissue for examining functional pathways, breast milk for metabolomics, and stool for metabolites and microbiome analysis. The offspring will have 6 infant/toddler visits at 6–12 weeks, 4 months, 6 months, 18 months, 2 and 3 years respectively. Thereafter, they will undergo comprehensive research visits (major visits) at 4–5 years, 6–9 years, 10–13 years, and 14–17 years. The major visits in children include detailed medical history, anthropometry, developmental assessment, socioeconomic and environmental assessments (food insecurity, family structure, and childcare), feeding and activity, biochemical tests, genetics/epigenetic testing, and ultrasound elastography. Electronic health records will be reviewed for additional clinical information. The primary analysis will constitute estimation of correlation coefficients between continuous variables. The planned study duration in this ongoing study is 23-years.

**Discussion:**

This is a life course study that that will examine biological and environmental risk factors for obesity and cardiometabolic risk from the intrauterine period to early childhood and adolescence in a population with high-risk of obesity and type 2 diabetes in the United States. The ETCHED study would also provide a unique opportunity to combine multi-omics and clinical data to create novel integrative models to predict the cardiometabolic risk associated with childhood obesity and possibly identify etiopathogenetic mechanisms and future targets of intervention.

**Trial registration number:**

ClinicalTrials.gov identifier: NCT03481829. Updated July 19, 2024, https://clinicaltrials.gov/study/NCT03481829?cond=ETCHED&rank=1.

## Background

The prevalence of childhood obesity and severe obesity continues to remain high and rising in the United States (US) with one-fifth of children and adolescents between the ages of 2–19 years currently having this chronic condition [1, 2]. A significant racial and ethnic disparity in obesity prevalence is also evident with children in vulnerable minority population groups, children who are of Hispanic ethnicity and/or American Indian/Alaska Native (AI/AN), bearing a major burden of disease [1–4]. With the increase in childhood obesity, there has also been a parallel and contemporaneous rise in the incidence of obesity-associated co-morbidities such as youth-onset type 2 diabetes (T2D) that was previously uncommon in the pediatric age group in the United States [5]. Based on the SEARCH for Diabetes in Youth study, a population-based registry of diabetes in youth (< 20 years) with surveillance, the incidence of clinically-diagnosed T2D has risen at a higher rate than that of type 1 diabetes (T1D) and for both types, the rates of increase have been more pronounced in minority youth particularly in Hispanic and AI/AN communities [6].

We have previously shown that in a cohort of AI/AN children living in the southwestern US, children with the most severe obesity had a 2- to 5-fold increased risk of developing diabetes by 20 years of age when compared to their peers with the least severe obesity, concluding that obesity severity is a key driver of the epidemic of youth-onset diabetes [7]. The disease course of youth with T2D is also more virulent compared to youth suffering from T1D, since they exhibit a higher risk for diabetes related micro vasculopathy [8]. Hence increased adiposity and subsequent obesity induced metabolic dysfunction manifesting early in the life-course may lead to adverse health outcomes in young adulthood including the risk of premature mortality [9].

Obesity and T2D are determined by a combination of biological and environmental factors, the most prominent of which is in utero exposure to maternal diabetes [10]. In a Southwestern US American Indian community, the offspring of mothers with diabetes have a greater risk of obesity and T2D than do offspring of fathers with diabetes or of mothers who developed diabetes after the pregnancy [11]. The increased risk of obesity and diabetes in the offspring was not entirely due to genetic susceptibility but was also attributable to the diabetic intrauterine environment [10, 11]. Intrauterine exposure to gestational diabetes was also associated with obesity in Mexican American children [12]. This phenomenon leads to a vicious cycle whereby the female offspring of a pregnant woman with diabetes during pregnancy are more likely to develop obesity and T2D before or during their child-bearing years, thus repeating the cycle across generations and leading to increasing prevalence of obesity and diabetes in youth [13, 14].

The fetal origins of adult disease theory describes the effect of adverse maternal conditions such as suboptimal nutrition during pregnancy resulting in structural and functional changes in the fetus (fetal programming). These changes predispose the offspring to cardiometabolic risk such as coronary heart disease, insulin resistance, and diabetes [15, 16]. The concept of Developmental Origins of Health and Disease (DOHaD) extends the fetal origins theory (critical period theory) and links early life biological and environmental exposures, to chronic disease risk during the life course [17].

The primary aim of the Early Tracking of Childhood Health Determinants (ETCHED) study is to examine the associations of maternal risk factors, including pre-pregnancy body mass index, gestational weight gain, and glycemia during pregnancy with offspring birth weight, length, and age/sex adjusted body mass index (BMI) percentile and z-score from birth until 2 years of age; a secondary objective includes studying these associations with BMI percentile and z-score from 2 to 18 years. Other secondary objectives study the role of maternal clinical, genetic, biochemical, lifestyle, and psychosocial factors during pregnancy in mediating the associations between maternal risk factors and birth weight of the offspring, and weight, adiposity, metabolic profile, and neurodevelopment; this during infancy, childhood, and adolescence. The ETCHED study will only enroll participants of Hispanic ethnicity and/or American Indian.

## Methods/design

### Study design

The Early Tracking of Childhood Health Determinants (ETCHED) study is a single-site longitudinal observational study being conducted by the National Institute of Diabetes and Digestive and Kidney Diseases (NIDDK), Phoenix Epidemiology and Clinical Research Branch (PECRB). Pregnant women are screened for eligibility and study enrollment began in April 2022 at the antenatal clinics at Valleywise Health Medical Center (VHMC) in Phoenix, Arizona. VHMC is the largest public hospital system in Maricopa County, Arizona, in the southwestern US.

### Eligibility criteria

Pregnant women aged 18 years or older, of AI/AN or of Hispanic race/ethnicity by self-report are eligible for participation. Participants must agree to continue with research study participation (both mother and their offspring) for at least 3-years post-delivery. Incarcerated women, women with a non-viable pregnancy, or those who are unable to consent for any reason, are excluded from participating in the study.

### Study timeline

The ETCHED study began enrolling participants in April 2022, and plans to enroll up to 750 mothers and their child (or children, if multiple gestation/pregnancy) for a total enrollment up to 1,500 persons over 5 years. The maternal/offspring dyad will be followed until the offspring’s 18th birthday. The planned study duration is 23-years with a completion date of April 2045.

The schedule of activities at research visits for both mother and child participants is shown in Table 1.

**Table 1 Tab1:** Schedule of activities for ETCHED

	Weeks Gestation				Child’s Age																				
	**9–12**	**13–28**	**≥ 29**	**Delivery**	**6–12 wks**	**4 mo.**	**6 mo.**	**1 yr**	**18 mo.**	**2 yrs**	**3 yrs**	**4 yrs**	**5 yrs**	**6 yrs**	**7 yrs**	**8 yrs**	**9 yrs**	**10 yrs**	**11 yrs**	**12 yrs**	**13 yrs**	**14 yrs**	**15 yrs**	**16 yrs**	**17 yrs**
**Maternal measures**																									
Demographics	X	X	X		X			X		X		X*		X*				X*				X*			
Medical History	X	X	X		X			X		X		X*		X*				X*				X*			
Medical Record Review	X	X	X	X	X			X		X		X*		X*				X*				X*			
Labs (Blood and urine)	X	X	X		X			X		X		X*		X*				X*				X*			
OGTT					X			X		X		X*		X*				X*				X*			
DNA/RNA	X		X					X		X		X*		X*				X*				X*			
Research blood and urine for storage	X	X	X		X			X		X		X*		X*				X*				X*			
Breastmilk (as available)					X			X		X															
Stool microbiome	X		X		X			X		X		X*		X*				X*				X*			
Vitals	X	X	X		X			X		X		X*		X*				X*				X*			
Questionnaires	X	X	X		X			X		X		X*		X				X*				X*			
**Child measures**				**Birth**	**6–12 wks**	**4 mo.**	**6 mo.**	**1 yr**	**18 mo.**	**2 yrs**	**3 yrs**	**4 yrs**	**5 yrs**	**6 yrs**	**7 yrs**	**8 yrs**	**9 yrs**	**10 yrs**	**11 yrs**	**12 yrs**	**13 yrs**	**14 yrs**	**15 yrs**	**16 yrs**	**17 yrs**
Medical History					X	X	X	X	X	X	X	X	X	X	X	X	X	X	X	X	X	X	X	X	X
Medical Record Review				X	X	X	X	X	X	X	X	X	X	X	X	X	X	X	X	X	X	X	X	X	X
Vital Signs											X	X	X	X	X	X	X	X	X	X	X	X	X	X	X
Limited Physical Exam and Anthropometrics					X	X	X	X	X	X	X	X	X	X	X	X	X	X	X	X	X	X	X	X	X
Cord Blood and Placenta				X																					
Questionnaires					X	X	X	X	X	X	X	X	X	X	X	X	X	X	X	X	X	X	X	X	X
Labs (Blood)								X				X*		X*				X*				X*			
Labs (Urine)												X*		X*				X*				X*			
DNA/RNA								X				X*		X*				X*				X*			
Stool for microbiome				X	X	X	X	X	X	X		X*		X*				X*				X*			
OGTT																		X*				X*			
Physical activity monitor wear																		X*				X*			
Transient elastography of liver												X*		X*				X*				X*			

*Measures occur at only one visit during timeframe

### Study objectives

The primary objective is to investigate the associations of maternal risk factors including pre-pregnancy body mass index (BMI), gestational weight gain, and glycemia with offspring’s birth weight, and weight and adiposity during infancy (0–24 months of age).

Secondary objectives of the ETCHED study include:

Studying the associations of maternal risk factors (pre-pregnancy BMI, gestational weight gain, and glycemia) with weight, adiposity, and physical growth patterns during childhood and adolescence (2–18 years of age).Studying the role of maternal clinical, genetic, biochemical, lifestyle, and psychosocial factors during pregnancy in mediating the associations between maternal risk factors and birth weight of the offspring, and weight, adiposity metabolic profile, and neurodevelopment during infancy, childhood, and adolescence.Examining the role of family, socioeconomic, and environmental factors influencing child growth patterns, body composition and neurodevelopment in infancy and childhood.To assess the frequency of hepatic steatosis in children and its association with BMI and biochemical alterations.Examining the relationship between maternal risk factors, early childhood exposures, and changes in gut microbiome during infancy, childhood, and adolescence.Studying the associations of maternal risk factors, including pre-pregnancy BMI, gestational weight gain, and glycemia and placental function, methylome, transcriptome, proteome and metabolome with weight, adiposity, and physical growth patters during childhood and adolescence (2–18 years of age).

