### Statistical analysis

The major analyses will be estimation of correlation coefficients between continuous variables, such as the correlations between maternal glycemia and offspring body size. To examine the roles of potential mediators on the relationship between maternal BMI, weight gain and glycemia with offspring body size, adiposity and metabolic outcomes, a series of linear regression models will be used in accordance with the coefficients mediation method described by MacKinnon et al. [20]. Analyses of the effect of maternal epigenetic or transcriptional changes in the serial samples will be performed using similar methods. Additional methods may also be used because statistical methods for mediation analysis are evolving.

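### Maternal genetic factors are listed among the mediators, but inherited genotype precedes the exposures and can only confound or modify their associations

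*Protocol article*

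**What the plan says.** The same list of mediators appears twice in the protocol article. The Background includes among the secondary aims "the role of maternal clinical, genetic, biochemical, lifestyle, and psychosocial factors during pregnancy in mediating the associations" between maternal risk factors and offspring outcomes. The Study objectives section repeats it as "Studying the role of maternal clinical, genetic, biochemical, lifestyle, and psychosocial factors during pregnancy in mediating the associations between maternal risk factors" and birth weight, later weight, adiposity, metabolic profile and neurodevelopment. The preceding item in that section names the risk factors as pre-pregnancy BMI, gestational weight gain and glycemia.

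The Statistical analysis section gives the method. To examine "the roles of potential mediators on the relationship between maternal BMI, weight gain and glycemia with offspring body size, adiposity and metabolic outcomes", it says that "a series of linear regression models will be used in accordance with the coefficients mediation method". A separate sentence follows: "Analyses of the effect of maternal epigenetic or transcriptional changes in the serial samples will be performed using similar methods". The section adds that further mediation methods may be used, without naming any.

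The Sample size and power calculation section also names genetic and epigenetic studies as two things. Nothing in the article says that inherited genotype is to be handled differently from the other listed factors.

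**The concern.** Mediation has a direction: the exposure changes the mediator, and the mediator changes the outcome. Inherited genotype cannot be changed by the mother's BMI, weight gain or glycemia. It can influence them, and because she passes part of it to her child it can also influence the child's size. That makes it a possible common cause, or a modifier of the exposure effect.

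The Background already treats heredity in this way. It reports that the excess risk in offspring of mothers with diabetes was not wholly explained by inherited susceptibility and was also due to the intrauterine environment. Genetics is the rival explanation there. In the objective it becomes a route by which the exposure acts. A reader given a percentage mediated by genetic factors would take as mechanism what is in fact confounding. The coefficients method cannot give a warning, because it uses only associations and these do not show which variable came first.

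**Working it through.** **Inputs.** The total standardised exposure-outcome effect is set to r(X,Y) = 0.15, the correlation called biologically meaningful in the Sample size and power calculation section. The analysed sample is 675 (750 less 10% attrition, Table 3). Genotype correlations r(X,G) and r(G,Y) are assumptions between 0.1 and 0.3.

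**The plan's own figure.** The plan gives no figure for mediation. Its power for r = 0.15 can be checked with Fisher's z and a two-sided alpha of 0.01 (sidedness is not stated): atanh(0.15) × √672 − 2.576 = 3.918 − 2.576 = 1.342, so power is 0.91. This agrees with the text (about 90%) and closely with Table 3 (0.92).

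**Formula.** With standardised variables and genotype G entered as the mediator:

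- a = r(X,G)
- b = [r(G,Y) − r(X,Y) × r(X,G)] / [1 − r(X,G)²]
- indirect effect = a × b; share = a × b / 0.15; direct effect = 0.15 − a × b

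| r(X,G) | r(G,Y) | b | a × b | Share called mediated | Direct effect |
|---|---|---|---|---|---|
| 0.1 | 0.1 | (0.1 − 0.015)/0.99 = 0.0859 | 0.0086 | 5.7% | 0.141 |
| 0.2 | 0.2 | (0.2 − 0.03)/0.96 = 0.1771 | 0.0354 | 23.6% | 0.115 |
| 0.3 | 0.2 | (0.2 − 0.045)/0.91 = 0.1703 | 0.0511 | 34.1% | 0.099 |

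If G is a cause of both X and Y, the true indirect effect through G is zero in every row.

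**Simulation at n = 675 (2,000 runs, Sobel test at 0.05).** G was generated as a cause of the exposure (path k) and of the outcome (path c), with a total slope of about 0.15.

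- k = c = 0.1: 6% called mediated, significant in 31% of runs.
- k = c = 0.2: 26%, significant in 99.7%.
- k = 0.3, c = 0.2: 40%, significant in 99.9%.

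The shares exceed those in the table at the larger values because c is a path coefficient. The implied r(G,Y) is c plus k times the direct effect; in the second case it is 0.2 + 0.2 × 0.11 = 0.222.

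**When the artefact does not arise.** If G is related to the outcome only through the exposure, then r(G,Y) = r(X,Y) × r(X,G) and b is zero. With r(X,G) = 0.2 and r(G,Y) = 0.03, b = (0.03 − 0.15 × 0.2)/0.96 = 0. Correlation with both variables is therefore not enough; G must be associated with the outcome given the exposure.

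**The case against.** The best defence is that the point rests on one word in a list of five. The objective speaks of factors during pregnancy, and Table 1 schedules maternal DNA/RNA sampling at both 9–12 and ≥29 weeks. The only molecular analysis that the Statistical analysis section explicitly ties to the mediation methods is of epigenetic and transcriptional changes, which can follow an exposure. No model with inherited genotype as mediator is written out, and other methods are allowed.

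This lowers the weight of the point without removing it. The article names genetic separately from epigenetic and transcriptional, so the word cannot simply be read as either of those. The allowance for further methods does not take genotype off the mediator list. It does mean that confounding *could* be reported as mediation, not that it certainly will be.

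Three stronger readings might be inferred, and the article does not support them:

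- *That factors measured at pregnancy visits cannot mediate weight gain.* The article does not define the exposure as total gain to delivery. Gain accrued by one visit can affect a factor measured at a later one. The exact window is detail that an article may leave to the full protocol or analysis plan.
- *That the exposure effect would be left uncorrected for genotype.* The same regressions give the genotype-adjusted direct effect (0.141, 0.115 and 0.099 above). The error lies in how the difference is labelled.
- *That any variable correlated with both exposure and outcome yields an indirect effect.* The zero case above shows otherwise.

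**Conclusion.** The point holds for inherited genotype. As written, the objective places it among the mediators of exposures that it precedes, and the stated method could present confounding as an indirect effect. The error of principle does not depend on any figure. Its size does: about 6% to 34% of a total effect of 0.15, under assumed genotype correlations of 0.1 to 0.3 and with genotype acting as a common cause. At the low end the share is small and would often not reach significance. The consequence is confined to what a secondary objective can conclude. The primary analyses, the sample size and the power figures are unaffected.

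**What to change.** In the Background and the Study objectives section, remove inherited genotype from the factors studied as mediators. In the Statistical analysis section, state that it is analysed as a confounder (by adjustment) and as an effect modifier (by interaction with the exposure).

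Keep epigenetic, transcriptional and biochemical factors as candidate mediators, with the condition that they are measured after the exposure and before the outcome. For weight gain, one way to meet this is to use gain up to one visit with the mediator taken at a later visit.

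The cost is a change of wording in three places. The samples and visits already scheduled suffice, and no new data are needed.

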### Study outcomes and data collection

The primary outcomes are birth weight, and weight, length, and age/sex adjusted BMI percentile and z-scores at 6–12 weeks, 4, 6, 12, 18, and 24-months. Secondary outcomes include BMI percentile and z-scores from 2 to 18 years of age, stool microbiome (microbial taxonomies, microbial pathways), hepatic steatosis and fibrosis, neurocognitive development, assessments of environmental and psychosocial status and biochemical measures for glycemia, lipids, renal, and liver function.

Data are collected either by in-person assessment, by review of medical records, by phone or other virtual media or a combination following the schedule of activities in Table 1. Data collected on mothers include demographics, anthropometric measures, socioeconomic and family environment history, medical history, obstetric history, laboratory evaluations, and biospecimens (blood, urine, stool, cord blood, placental tissue, and breast milk). Data collected on offspring include demographics, birth history, socioeconomic history such as living situation, childcare arrangements, parental education and employment, food insecurity, cultural practices during pregnancy, medical history, assessments of lifestyle habits such as eating and activity patterns, sleep, perceived stress, laboratory evaluations, and biospecimens (blood, urine, and stool). DNA and RNA data are collected on both mothers and offspring. The data collected in ETCHED are summarized in Table 2. Some of the information related to medical history of mothers and/or offspring is obtained by direct interview, by review of medical records, or both.

**Table 2 Tab2:** Data collected in ETCHED

Participant	Type	Collected data
Mother	Demographic, socioeconomic and family environment history	• Age, race/ethnicity, marital status, approximate age of child’s father, father’s race ethnicity, father’s diabetes status • Highest level of education of parents, family size, family employment history, family income, family ownership, family hardships, household characteristics • Childcare arrangements
	Medical record review	• Clinical information, laboratory and radiological information • This includes demographic, anthropometric, clinical history, results of imaging studies, and biochemical data (will focus on periodic measures related to glycemia).
	Medical history	• Underlying health conditions, new illnesses or hospitalizations between visits, maternal history of COVID-19 infection
	Obstetric history	• Pre-pregnancy weight, delivery date(s), APGAR score, sex, weight, length, gestational age, prenatal and perinatal history, pregnancy outcomes
	Laboratory evaluations	• From blood: blood complete blood count, HbA1c, fasting glucose and insulin, adiponectin, TNF, IL-6, folate, CRP, and cytokines, biological markers for obesity and metabolic dysfunction, liver function tests, serum cholesterol, triglycerides, HDL and LDL cholesterol, apolipoproteins • Oral glucose tolerance test in the research clinic postpartum
	Biospecimens	• Blood for DNA, RNA • Stool for microbiome analysis • Breastmilk
	Mother’s procedures	• Physical exam [height, weight, waist circumference (non-pregnant) and blood pressure measurement] • Questionnaires: Unmet Social Support, Modifiable Activity Questionnaire, Pittsburg Sleep Quality Index, Adverse Childhood Experience, BLOCK-2000, Food Insecurity Questionnaire, Eating Behaviors (EARLY), Cohen’s perceived Stress Scale, Short Acculturation Scale for Hispanics (SASH) if appropriate, and cultural consideration survey
Infant	Birth history (by medical record review)	• Neonatal history such as mode of delivery, birth, weight, height, and head circumference, gestational age, APGARS, neonatal/perinatal complications, congenital anomalies
	Medical history	• Mother will be asked about: vaccination history, history of illness, including COVID diagnosis, antibiotics use, hospitalizations, ED visits, any new diagnosis.
	Medical record review	• Clinical, laboratory, and radiological information
	Laboratory evaluation	• Blood will be drawn for CBC, HbA1c, insulin, and lipids
	Biospecimens	• Cord blood for Hba1c, insulin, biomarkers such as c-peptide, leptin, adiponectin, TNF-alpha; other novel metabolomics, genetic and epigenetic tests. SARS-COVID 19 antibody • Placenta tissue for subsequent analysis of placenta function, methylome, transcriptome, proteome, metabolome, histopathology and histochemistry • Blood draw for DNA and RNA • Meconium and stool for microbiome analysis
	Procedures	• Physical exam: length, weight, head circumference • Congenital anomalies evident on clinical exam • Questionnaires that the mother will complete on behalf of the infant: cultural feeding practices, Infant consumption of food frequency, Infant feeding styles, Infant sedentary behavior, Breastfeeding formula feeding, Parent’s evaluation of development Status (PEDS) questionnaire, and Modified Checklist for Autism in Toddlers, Revised (M-CHAT-R), BLOCK Kids 2–7 Food Frequency questionnaire
Child	Medical history	• Vaccination history, history of intermittent illness, included COVID diagnosis, antibiotics use, hospitalizations, ED visits, new diagnosis
	Medical record review	• History of inter-current illness, antibiotics use, ED visits, hospitalizations, surgeries, other missed visits information such as anthropometric measures, blood pressure, lab results of tests that are part of a research and developmental milestones
	Laboratory measures	• Blood will be drawn for fasting glucose, CBC, HbA1c, OGTT (> 10 years), insulin, lipids, AST, ALT, bilirubin, cytokines and other biological markers for obesity and metabolic dysfunction • Urine will be collected for urine dip analysis and urine ACR
	Biospecimens	• Blood for DNA/RNA • Stool for microbiome analysis
	Procedures	• Physical exam: height, weight, head circumference (up to 36 months old), waist circumference, limited physical exam including Tanner staging • Questionnaires: completed by mother or guardian on behalf of the child until child is able to answer the questions in the survey independently or with parent’s help: PEDS, Netherlands Physical Activity Questionnaire, MAQ Adolescents Activity Questionnaire, BLOCK Kids diet questionnaires • Transient elastography (hepatic steatosis) in children 4 years or older: will obtain liver stiffness measurement (LS) and controlled attenuation power (CAP) measure • Accelerometer: will measure physical activity over a 7 day period, except during periods of bathing or swimming • Oral glucose tolerance test performed when children are > = 10 years of age: will collect FPG and 2-hr PG

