### **Analysis of the** primary outcomes

As described above, to examine associations among maternal risk measures, and offspring weight and body size, scatterplots and grouped box plots will be constructed to examine assumptions of linearity, symmetry, and homoscedasticity. To model changes in childhood BMI over time, we will use mixed effects models to fit a piecewise growth curve model which predicts childhood BMI as a function of time.

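### Postnatal weight and length are primary outcomes without age standardisation, which attenuates the correlations at the 6–12 week visit; its size depends on how widely visit ages spread

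*Protocol article*

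**What the plan says.** All references are to the protocol article.

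- **Outcomes.** Study outcomes and data collection gives the primary outcomes as birth weight plus "weight, length, and age/sex adjusted BMI percentile and z-scores at 6–12 weeks, 4, 6, 12, 18, and 24-months". The adjustment qualifies BMI and not the two measures before it. The primary aim in the Background is worded similarly: "offspring birth weight, length, and age/sex adjusted body mass index (BMI) percentile and z-score from birth until 2 years of age". That sentence does not name postnatal weight, but the Study objectives section does include weight during infancy.
- **Timing.** The Abstract lists "6 infant/toddler visits at 6–12 weeks, 4 months, 6 months, 18 months, 2 and 3 years respectively". Only the first of these is a range. Table 1 also uses 6–12 weeks as one column.
- **Analysis.** Statistical analysis states: "The major analyses will be estimation of correlation coefficients between continuous variables, such as the correlations between maternal glycemia and offspring body size". The one model in which time appears, under Analysis of the primary outcomes, uses "mixed effects models to fit a piecewise growth curve model which predicts childhood BMI as a function of time", and so covers BMI only.
- **Records.** Table 1 schedules a child medical record review at every infant visit. Table 2 mentions "other missed visits information such as anthropometric measures", but in the Child rows and not the Infant rows.

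**The concern.** The first postnatal visit may fall anywhere in a six-week span, so the oldest infants can be twice as old as the youngest. Infants grow quickly at this age. Two infants with the same growth status, one measured at 6 weeks and one at 12, would enter the same correlation with different raw weights and lengths. BMI is protected by its adjustment; weight and length, as defined, are not.

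If visit timing has nothing to do with the maternal exposure, this is noise in the outcome. The correlation is attenuated, and the chance of detecting the effect the investigators call biologically meaningful (a correlation of 0.15) is lower than for an age-standardised measure. Birth weight is not affected.

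**Working it through.** **Inputs from the article** (Sample size and power calculation, Table 3): 750 pairs recruited, 675 after 10% attrition; alpha 0.01; target correlation 0.15; power stated as about 90% in the text and 0.92 in the table. Sidedness is not stated; two-sided is assumed.

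**Step 1: the planned figure.** By Fisher's z, power = Φ(atanh(r)·√(n − 3) − z), with z = 2.576 for two-sided alpha 0.01. For r = 0.15 and n = 675: atanh(0.15) = 0.1511, √672 = 25.92, product 3.918; 3.918 − 2.576 = 1.342; Φ = 0.910. This agrees with the stated figure to within about a point. (Alpha 0.0125 gives 0.922, closer to the table. That is a separate matter and does not change what follows.)

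**Step 2: attenuation.** Let g be growth per week, τ the SD of age at visit and σ the SD of size at a fixed age. Put q = g·τ/σ. If visit age is unrelated to the exposure and growth is roughly linear across the window, the observed correlation is r/√(1 + q²), and timing accounts for q²/(1 + q²) of the outcome variance.

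**Assumed inputs, not in the documents:**
- weight gain g = 0.10–0.25 kg per week; same-age SD σ = 0.5–0.7 kg;
- τ = 6/√12 = 1.73 weeks if ages fill 6–12 weeks evenly; τ = 0.75 weeks if visits cluster; τ = 1.0 as an intermediate case.

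One case in full, with g = 0.20, σ = 0.6, τ = 1.73: g·τ = 0.346 kg; q = 0.346/0.6 = 0.577; √(1 + 0.333) = 1.155; observed r = 0.15/1.155 = 0.1299; power 0.79. Timing accounts for 0.333/1.333 = 25% of the variance. For 90% power, about 875 analysed pairs would be needed, against about 655 at r = 0.15.

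**Step 3: the range for weight** (observed r, then power at n = 675):

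| Age SD (weeks) | g 0.10, σ 0.7 | g 0.20, σ 0.6 | g 0.25, σ 0.5 |
|---|---|---|---|
| 1.73 (even spread) | 0.1456, 0.89 | 0.1299, 0.79 | 0.1134, 0.65 |
| 1.0 | 0.1485, 0.90 | 0.1423, 0.87 | 0.1342, 0.82 |
| 0.75 (clustered) | 0.1491, 0.91 | 0.1455, 0.89 | 0.1404, 0.86 |

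With an even spread, the share of variance due to timing runs from 0.061/1.061 = 6% to 0.75/1.75 = 43%.

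**Step 4: length.** Assuming 0.5–0.9 cm per week and a same-age SD of 2.0–2.5 cm, power is 0.69–0.87 for an even spread and 0.87–0.90 for clustered visits.

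**Step 5: with age standardisation,** q = 0 and power returns to 0.91.

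**The case against.** The strongest reply is that this is a condensed article. How a measurement is standardised, and whether age enters as a covariate, may be settled in the full protocol or analysis plan, which are not at hand. Nowhere does the article say that the correlations will be unadjusted. That caution stands as far as the analysis goes. It does not dispose of the outcome definition, because the article does address age adjustment and gives it to one of three body-size measures. If the full documents adjust all three, the published definition still needs correcting.

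Four stronger readings are tempting and are not supported:

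- **That the primary correlations are biased.** A spurious correlation needs visit age to be related to the maternal exposure. One can imagine exposure-related attendance, but nothing in the article shows it. Without it, the effect is attenuation only.
- **That every postnatal visit is affected.** The later infant visits are given as single ages with no window, so there is no stated spread to work from.
- **That the power statement is wrong.** Table 3 gives power for a correlation of stated size between any two variables. The loss shown here arises only if 0.15 is taken as the correlation at a fixed age.
- **That infant values from missed visits will come from clinic records at arbitrary ages.** The phrase on missed visits is in the Child rows of Table 2; the Infant rows do not say it.

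It is also fair to object that z-scores are not the only remedy. Adjusting for exact age would serve as well.

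**Conclusion.** The point holds in limited form. Followed as written, the article correlates raw weight and length at the 6–12 week visit with the maternal exposures, and variation in age at measurement makes those correlations noisier and smaller than they need be. Whether the loss matters in practice turns mainly on how far actual visit ages spread: it is material if they fill the window and slight if they cluster. The figures depend on assumed growth rates, same-age SDs and age spread, and on timing being unrelated to exposure, so they indicate a plausible range and not a demonstrated shortfall. The case for acting is that the noise is avoidable at almost no cost.

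**What to change.** In Study outcomes and data collection, define postnatal weight and length as age- and sex-standardised z-scores computed from the exact date of measurement, as for BMI. Alternatively, keep the raw measures and state in Statistical analysis that their correlations with maternal exposures will be partial correlations adjusted for exact age and sex. Either choice matters most at the 6–12 week visit. Add that any value taken from medical records is handled by its true measurement date and not the nominal visit.

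The cost is a sentence or two and a routine calculation. Birth date, measurement date and sex are already needed for the BMI z-score, so no new data or visits are required. The wording should be settled before the primary analysis.
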